## Abstract

**Background:**

Hepaticojejunostomy is commonly performed in hepato-bilio-pancreatic surgery, particularly during pancreaticoduodenectomy. The purpose of this study is to evaluate the safety and efficiency of two commonly applied suture techniques (the interrupted versus the continuous suture technique) in patients undergoing a hepaticojejunostomy during pancreatoduodenectomy.

**Methods:**

The HEKTIK trial is a multicenter, randomized controlled, patient-blinded surgical explorative trial with two parallel study groups. An adaptive sample size design was chosen: First, 100 patients scheduled for surgery including a hepaticojejunostomy will be randomized 1:1 either to the interrupted suture technique or the continuous suture technique after informed consent. Based on this data, needed sample size will be adjusted.

The primary endpoint will be the occurrence of anastomotic leakage of hepaticojejunostomy, defined as bilirubin concentration in the drain fluid at least 3 times the serum bilirubin concentration on or after postoperative day 3 or as the need for radiologic or operative intervention resulting from biliary collections or bile peritonitis (according to the definition of ISGLS). Further perioperative parameters like other morbidities as well as duration and costs of the hepaticojejunostomy will be analyzed as secondary outcomes.

**Discussion:**

Until now there are no randomized controlled comparative data of these two suture techniques for hepaticojejunostomy. The HEKTIK trial will investigate the yet unanswered question of whether the interrupted suture or the continuous suture technique has advantages performing a hepaticojejunostomy during pancreatoduodenectomy.

**Trial registration:**

German Clinical Trials Register DRKS00024395. Registered on 01 February 2021.

**Supplementary Information:**

The online version contains supplementary material available at 10.1186/s13063-022-06427-1.

## Background

Hepaticojejunostomies represent a common step during pancreatic and liver surgery including partial pancreatoduodenectomy, major liver resections, and bile duct resections. Overall, a hepaticojejunostomy is considered as a safe procedure with low rates of postoperative complications including a leakage rate of 2.3% to 5.6% [1, 2]. However, failure of this anastomosis leads to considerable consequences with a high risk of prolonged hospitalization and the need for interventional drainage or re-laparotomy, which is associated with high morbidity and mortality, even in high volume centers [3, 4]. Known risk factors for leakage are previous chemoradiation, preoperative biliary drainage, impaired liver synthesis capacity, malnutrition, obesity, and anastomosis at the level of hepatic duct bifurcation [1].

However, leakage of a hepaticojejunostomy could always be associated with the surgical technique used. There are especially two common techniques used for hepaticojejunostomy: the interrupted suture technique and the continuous suture technique. According to a current national survey in Germany 56% of the participating hospitals stated that they use both techniques for performing a hepaticojejunostomy depending on the surgical sites, while 40% of the hospitals adhere always to one of the mentioned two techniques. These results show a relevant heterogeneity of the techniques used among hospitals in Germany [5]. There is an ongoing debate between advocates of both techniques, who argue with universal use (also for small ducts) and a potentially lower stenosis rate for the interrupted suture technique and with a better sealing of the anastomosis and operative time saving for the continuous suture technique.

Despite the frequent necessity of hepaticojejunostomies in surgery and the relevant consequences for the patient with leakage, there are no randomized studies to compare the different surgical techniques. For this reason, the presented randomized controlled multicenter trial was initiated to assess whether there is a significant difference in the occurrence of anastomotic leakage between the two groups interrupted suture versus continuous suture technique for performance of a hepaticojejunostomy during pancreatoduodenectomy.

#### Protocol amendments

The study protocol was adapted once as part of revision for this publication (version 2.0).

### Trial design and study setting

The objective of the HEKTIK trial is to investigate whether there is a significant difference in the occurrence of anastomotic leakage between the two groups interrupted suture versus continuous suture technique for performance of a hepaticojejunostomy during pancreatoduodenectomy. The study is designed as a randomized controlled, national (Germany), patient-blinded multicenter trial with the performance of a hepaticojejunostomy in interrupted suture technique in one arm and in continuous suture technique in the other arm. To homogenize patient collective and the risk profile for occurrence of anastomotic leakage of hepaticojejunostomy only patients with pancreatoduodenectomy were included. Until now, there is only the institution of the study coordinators, that recruits patients for the HEKTIK trial. Further high-volume centers are planned to initiate soon.

### Aim of the study and study endpoints

Primary endpoint of this trial is the prevelance of an anastomotic leakage of the hepaticojejunostomy, as it was defined by the International Study Group of Liver Surgery (ISGLS) in 2011 [6]:*“After evaluation of the postoperative course of bilirubin levels in the drain fluid of patients who underwent hepatobiliary and pancreatic operations, bile leakage was defined**as bilirubin concentration in the drain fluid at least 3 times the serum bilirubin concentration on or after postoperative day 3**or**as the need for radiologic or operative intervention resulting from biliary collections or bile peritonitis.”* [6]

The secondary endpoints are:Total operative timePostoperative increase in cholestasis parameters (γGT, alkaline phosphatase, bilirubin)Reoperation rate (during hospital stay and at 3 and 12 months postoperative)Reintervention rate (e.g., ERCP, PTCD) (during hospital stay and at 3 and 12 months postoperative)Morbidity (during hospital stay and at 3 and 12 months postoperative)The recorded morbidity includes:*Clavien-Dindo classification:* see Table 1 [7].*Comprehensive complications index (CCI):* The CCI is calculated as the sum of all complications that are weighted for their severity (multiplication of the median reference values from patients and physicians). The final formula yields a continuous scale to rank the severity of any combination of complications from 0 to 100 in a single patient [8]*Postoperative pancreatic fistula (POPF):* defined as a drain output of any measurable volume of fluid with an amylase level > 3 times the upper limit of institutional normal serum amylase activity, associated with a clinically relevant development/condition related directly to the postoperative pancreatic fistula [9]Mortality (during hospital stay and at 3 and 12 months postoperative)Duration of the hepaticojejunostomy performanceMaterial costs for the hepaticojejunostomyStenosis rate of hepaticojejunostomy at 3 and 12 months postoperative

**Table 1 Tab1:** Clavien-Dindo classification

Grade	Definition
Grade I	Any deviation from the normal postoperative course without the need for pharmacological treatment or surgical, endoscopic, and radiological interventions. Allowed therapeutic regimens are drugs such as antiemetics, antipyretics, analgesics, diuretics, electrolytes, and physiotherapy. This grade also includes wound infections opened at the bedside.
Grad II	Requiring pharmacological treatment with drugs other than such allowed for grade I complications Blood transfusions and total parenteral nutrition are also included
Grade III	Requiring surgical, endoscopic or radiological intervention
Grade IIIa	Intervention not under general anesthesia
Grad IIIb	Intervention under general anesthesia
Grade IV	Life-threatening complication requiring IC/ICU management
Grade IVa	Single organ dysfunction (including dialysis)
Grade IVb	Multiorgan dysfunction
Grade V	Death of patient

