### Surgical technique

The hepaticojejunostomy will be performed as a part of pancreatoduodenectomy and can be placed on the same jejunal loop as the pancreatojejunostomy or on a second jejunal loop.

The common preparation before suturing the hepaticojunostomy includes an opening of the hepatic duct with corner sutures and an antimesenterical jejunal incision. After the corner sutures are placed at the hepatic duct, the diameter of the ductus hepaticus is measured in mm and documented in the CRF.

The further procedure depends on the randomized technique:Interrupted suture technique: with this technique both the posterior and the anterior walls are performed single-rowed using interrupted stitches.Continuous suture technique: with this technique both the posterior and the anterior walls are performed single-rowed using continuous sutures.

There are no specifications for the suture material and the number of sutures used, but these data will be documented in the CRF. If an anastomotic leakage is detected intraoperatively, any number of interrupted sutures may be added to the hepaticojejunostomy. The measurement of the duration of the hepaticojeunostomy begins with the first suture (excluding the corner sutures of the hepatic duct) and ends with the cutting of the last thread, which is necessary to complete the hepaticojeunostomy. The application of an abdominal drainage near the hepaticojejunostomy is standard in our department and is recommended, but not mandatory.

Used suture material, number of sutures, number of interrupted stiches, number and place of abdominal drains, and the time for hepaticojejunostomy are documented in the CRF. In addition, the surgeon’s experience performing hepaticojejunostomies is recorded and documented in the CRF.

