### Randomization and blinding

After the inclusion criteria have been confirmed and the patient's consent has been obtained preoperatively by trained medical staff as well as exclusion criteria (e.g., no performance of a hepaticojejunostomy due to irresectability of the pancreatic tumor) have been excluded intraoperatively, randomization will be carried out intraoperatively immediately before the hepaticojejunostomy is performed. Randomization only takes place if the surgeon considers the present situs to be suitable for both suturing techniques and the ductus hepaticus is at least 5 mm (Fig. 1).

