The screening form contains demographic data including basis data, disease course, and comorbidities as well as preoperative blood results (including hemoglobin, white blood cells, creatinine, albumin, serum c-reactive protein, and liver enzymes). In the surgical form data about the operation like duration and kind of surgery as well as data about the hepaticojejunostomy (duration, suture material, information about the hepatic duct) is recorded. The postoperative forms include always the documentation of morbidity and mortality as well as at POD 1 and 3 laboratory results (including hemoglobin, white blood cells, creatinine, albumin, serum c-reactive protein, Quick, bilirubin as well as liver enzymes and cholestasis parameters) and the bilirubin concentration in the abdominal drain being close to the hepaticojejunostomy. At discharge histological results and length of hospital stay are additionally documented.

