### Statistical considerations and sample size calculation

Literature was systematically reviewed to identify all published data to this topic (see Supplementary Fig. 1). There were no randomized controlled trials and only one retrospective analysis from Japan, which compared the interrupted suture technique with the continuous suture technique in the setting of liver transplantations [11]. However, these data are not suitable for a meaningful sample size calculation, as the leakage rates of this reported trial come from a different setting and seem to be high compared to data derived mainly from hepaticojejunostomies only or as part of a pancreatoduodenectomy (5.6% using interrupted sutures [1] and 2.3% using both techniques [2], respectively).

Therefore, an adaptive sequential sample size design was chosen: The sample size per patient group was set exploratively at a group size of 50 patients. Total sample size was 100 patients. The prevalence of the primary endpoint in the 100 patients examined then forms the data basis for an adequate further sample size analysis and consequently for a sample size adjustment. To proceed the study with the then new calculated sample size, some criteria have to be met: First, the absolute difference in the primary endpoint must be at least 1% to justify clinical relevance of the study. Second, the calculated sample size per group should not exceed 1000 patients in order to be able to meaningfully end the study.

Due to the design with multiple testing an error correction will be performed in statistical analysis. Due to the lack of reliable data in the literature, this adaptive design offers the best opportunity to get meaningful data with adequate power.

Statistical analysis will be performed using SPSS software. An intention-to-treat and a per-protocol-analysis will be used for the analysis of the primary outcome. Comparisons of metric and ordinal data will be calculated with the Student *t*-test or Mann-Whitney *U* test. The chi-square test was used for categorical data. Statistical significance will be set at *p* < 0.05.

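### Total operative time includes surgery done before randomisation, which adds variance (not bias) to an unadjusted secondary comparison

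*Protocol article*

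**What the plan says.** All references are to the protocol article.

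- **Aim of the study and study endpoints.** Total operative time opens the list of secondary endpoints: "The secondary endpoints are:Total operative timePostoperative increase in cholestasis parameters". No start or stop point is given and no ranking among secondary endpoints is stated. Duration of the hepaticojejunostomy is a separate item in the same list.
- **Randomization and blinding.** Allocation takes place during surgery: "randomization will be carried out intraoperatively immediately before the hepaticojejunostomy is performed". By then irresectability has been ruled out and the duct has been found to be at least 5 mm wide.
- **Surgical technique.** The clock for the anastomosis "begins with the first suture (excluding the corner sutures of the hepatic duct) and ends with the cutting of the last thread".
- **Study visits and data collection.** The length of the operation is recorded: "In the surgical form data about the operation like duration and kind of surgery". A clock time of randomisation is not among the items named.
- **Statistical considerations and sample size calculation.** "Comparisons of metric and ordinal data will be calculated with the Student *t*-test or Mann-Whitney *U* test"; "Statistical significance will be set at *p* < 0.05". No covariate adjustment is mentioned. The first stage has 50 patients per group.
- **Background.** Advocates of one technique claim "operative time saving for the continuous suture technique".

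**The concern.** Only what happens after allocation can differ because of the suture technique. Exploration and everything else completed before the hepaticojejunostomy is a baseline quantity. If total operative time starts at the usual point, that baseline quantity is part of the outcome, and its patient-to-patient variation enters the standard error of the arm comparison without adding information about the technique.

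What is at stake is precision. Operative time saving is one of the arguments the protocol itself reports in the debate between the techniques. A comparison of total time at 50 per group could easily return an inconclusive result even if a modest saving existed, and a reader could mistake that for evidence that the technique makes no difference to operating time.

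**Working it through.** **Is there a figure in the plan to reproduce?** No. The 50 per group (2 × 50 = 100) was set exploratively, and no power, effect or SD is stated for operative time. The arithmetic below is illustrative.

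**Step 1: split the outcome.** Write total time T = A + B, where A is time before randomisation and B is time after it.

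- Expected arm difference: A is fixed before allocation, so randomisation gives it the same expectation in both arms. The expected difference in T equals the expected difference in B.
- Variance: Var(T) = Var(A) + Var(B) + 2 Cov(A, B). This exceeds Var(B) unless A and B are negatively related with Cov(A, B) below −Var(A)/2.

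The target is the same in both analyses; the noise is normally larger with T.

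**Step 2: size of the noise.** Inputs from the article: 50 per group, alpha 0.05. Assumed: two-sided test, true saving 10 minutes, SD of T 60-100 minutes, SD of B 30-50 minutes.

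SE of the difference = SD × √(2/50) = SD × 0.2. Power is from the noncentral t distribution with 98 degrees of freedom and noncentrality 10/SE.

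| Outcome | SD (min) | SE (min) | Power for 10 min |
|---|---|---|---|
| Total time | 60 | 12 | 13% |
| Total time | 80 | 16 | 9.5% |
| Total time | 100 | 20 | 8% |
| Time after randomisation | 30 | 6 | 38% |
| Time after randomisation | 40 | 8 | 24% |
| Time after randomisation | 50 | 10 | 17% |

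The variance ratio runs from (60/50)² = 1.4 to (100/30)² = 11, so the gain may be modest or large.

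**Step 3: one worked decomposition.** Assume independent A and B with SDs 60 and 30. Then SD(T) = √(60² + 30²) = √4500 = 67 minutes. Power for 10 minutes is 11% with T and about 38% with B.

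**Step 4: check for bias.** Using the Step 3 SDs, 20,000 trials with 50 per group were simulated and analysed by t-test on T.

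- No true effect: rejection rate 5.2%, mean difference about 0 (−0.09 minutes).
- True 10-minute saving: mean estimate 9.9 minutes.
- SD of the chance difference between arm means: 13.5 minutes, matching 67 × 0.2 = 13.4. The test's standard error already contains it.

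**Step 5: the endpoint already planned.** Randomisation requires a duct of at least 5 mm, and Surgical technique places the measurement after the corner sutures. The anastomosis clock starts with the first suture after those, so hepaticojejunostomy duration lies wholly after randomisation. With an assumed SD of 8-10 minutes and 50 per group, power is over 99% for a 10-minute difference and about 70-88% for 5 minutes.

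**The case against.** **The time question is already answered elsewhere.** Hepaticojejunostomy duration is a secondary endpoint with a defined start and stop, and Step 5 suggests it would detect a plausible saving far better than either version of operating time. The abstract names it and does not name total time. This stands for the narrow question of how long the anastomosis takes. It does not settle whether a saving carries through to the end of the operation, which is the question total time is there to answer.

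**The proposed analysis is itself weak.** At 17-38% power a 10-minute saving would still usually be missed at the first stage. This is true, and it is a reason to call the change an improvement and not a rescue. The comparison also uses only the first 50 per group. At the 1000-per-group ceiling, total time would have 70-96% power for SDs of 60-90 minutes.

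**Adjustment belongs in the analysis plan, and total time is a legitimate measure.** The article is condensed, and a fuller plan could adjust. However, the article does name the test for metric data, and that test is unadjusted.

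**Stronger readings that the article does not support.** A reader might infer three things:

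- *That resection time could pass for a technique effect.* Time before allocation is independent of arm under concealed randomisation, and Step 4 shows no bias and a false-positive rate near 5%.
- *That the clock runs from skin incision.* This is the usual convention, but no start point is given.
- *That most of the operation, or most of its variation, precedes randomisation.* This is plausible, but there are no operative times in the article, and the order of the pancreatic anastomosis relative to the biliary one is not stated.

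**Conclusion.** The point holds as a matter of efficiency on one secondary endpoint. The stated comparison of total operative time carries pre-allocation variation that the technique cannot affect, and an analysis with the same expected difference and normally a smaller standard error is available. There is no systematic bias and no inflation of type I error. The primary endpoint, the sample size adjustment and safety are untouched.

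The direction rests on the timing of randomisation stated in the article, on the usual reading of total operative time, and on times before and after randomisation not being strongly negatively related. The size (about 8-13% against 17-38% power for 10 minutes at 50 per group) rests entirely on assumed SDs and an assumed effect. Low priority, but worth doing because it costs so little.

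**What to change.** 1. Add the clock time of randomisation to the surgical form, and define the start and stop of total operative time.
2. State in the analysis section that total operative time is analysed by linear regression on arm, adjusted for the time elapsed before randomisation. The alternative is to test time from randomisation to closure. Both target the same mean difference but are not identical: the second fixes the coefficient of pre-randomisation time at 1, while the regression estimates it. Choose one in advance.
3. Report unadjusted total operative time by arm descriptively.
4. Keep hepaticojejunostomy duration as the main technique-time endpoint.

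**Cost.** One form field and one or two sentences, with no extra patients or procedures. Recruitment began in March 2020, so the time would have to be retrieved for patients already operated. The article does not show that a record of it exists, so it may be incomplete. If the full form already captures it, only the analysis sentences are needed.

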### Study population (inclusion and exclusion criteria)

All patients scheduled for elective hepaticojejeunostomy during pancreatoduodenectomy will be screened consecutively for eligibility and will be informed about the HEKTIK trial. The diameter of the ductus hepaticus be anastomosed must be at least 5 mm, which is determined by measuring the ductus hepaticus intraoperatively. There are the following further general inclusion criteria: age equal to or older than 18 years, American Society of Anesthesiologists (ASA) score I–III, and a completed written informed consent form (Fig. 1).

**Fig. 1 Fig1:**
[figure not shown]
Flow chart of the HEKTIK trial. POD, postoperative day

### Patient withdrawal criteria

Patients are free to stop their trial participation at any time and without giving reasons for their decision. When a trial participant withdraws his/her informed consent, he/she is asked to decide whether his/her data captured so far may be analyzed or if it should be discarded. In addition, if intraoperatively the diameter of the ductus hepaticus is less than 5 mm or in the surgeon’s opinion there is only one possible technique or one better technique for the patient, the trial participation will be stopped for this patient (Fig. 1). In this case, the patient will not be randomized, and the reason for screening failure must be recorded in the screening log. All randomized patients, including those with premature trial termination, will be included in the final analysis.

